#### Suspension criteria

Patient demanding suspensionSafety reasons, such as treatment-related adverse eventsLoss to follow-up or a lack of complete data

### Strategies to improve adherence to interventions {11c}

During the RCT, participants will receive an incentive of reduced costs for blood tests and ultrasound.

### Relevant concomitant care permitted or prohibited during the trial {11d}

Any treatment or change outside of the study intervention will be monitored throughout the trial.

### Provisions for post-trial care {30}

No special provisions are offered.

### Outcomes {12}

#### Primary outcome measure

The primary outcome measure is the clinical pregnancy rate: the ratio of the clinical pregnancy (intrauterine gestation sac with a fetal heart beat) number to the number of patients who received embryo transfer.

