#### Endometrial preparation

All the included patients will undergo an HRT cycle for endometrial preparation. Treatment will start on day 2 or day 3 of menstruation with oral Femoston (estradiol 2 mg po tid). After approximately 10–12 days of estrogen treatment, a transvaginal ultrasound will be performed to measure the endometrial thickness. Two procedures for further treatment depending upon the endometrial thickness are listed as follows:If the endometrium thickness is not less than 8 mm, patients will continue to take Femoston (estradiol tablet). On days 16–20 of the HRT cycle, patients will be changed over to receive oral Femoston (2 mg estradiol and 10 mg dydrogesterone tablet, po tid) and intramuscular injections of progesterone (60 mg qd) to transfer the endometrium into the secretory phase.If the endometrium thickness is less than 8 mm, the dose of oral Femoston (estradiol tablet) will increase to 8 mg until the endometrium thickness reaches 8 mm. On days 18–20 of the HRT cycle, Femoston (2 mg estradiol and 10 mg dydrogesterone tablet, po tid) and progesterone (60 mg qd) will be administered to transfer the endometrium into the secretory phase. If the endometrium thickness is still less than 8 mm, it should be discussed with patients whether to proceed with FET or abandon the protocol.

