#### Secondary outcome measures

Secondary outcome measures are the miscarriage rate and LBR.

Miscarriage rate: The ratio of the number of nonviable pregnancies before 12 weeks of gestation to the number of clinical pregnancies.

LBR: The ratio of the number of normal fetuses delivered after 28 weeks of gestation to the number of patients who received embryo transfer.

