### Participant timeline {13}

The participant timeline is shown in Table1.

**Table 1 Tab1:** SPIRIT figure: schedule of enrollment, interventions, and assessments

Timepoint	Study period					
	Enrollment			Post-allocation		
	T1	T2	T3	T4	T5	T6
	Day of progesterone supplementation	Period of HRT-cycle	Day of embryo transfer	14 days after transfer	30/42 days after transfer	After delivery

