## Assignment of interventions: blinding

### Who will be blinded {17a}

This study is an open trial. Both patients and researchers know the group assignments in the trial and only the statisticians are blinded to the grouping.

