### Methods in analysis to handle protocol non-adherence and any statistical methods to handle missing data {20c}

Data will be analyzed following the ITT principle. Missing data will be analyzed. The imputation of missing values is not intended, although multiple imputations might be used within sensitivity analyses assuming data are missing at random.

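### Clinical pregnancy and live birth are counted per woman transferred, which conflicts with the stated ITT analysis for any randomised woman who has no transfer

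*Protocol article*

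**What the plan says.** All references are to the protocol article.

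- **Primary outcome measure:** the clinical pregnancy "number to the number of patients who received embryo transfer".
- **Secondary outcome measures, live birth:** "The ratio of the number of normal fetuses delivered after 28 weeks of gestation to the number of patients who received embryo transfer".
- **Methods to handle non-adherence and missing data {20c}:** "Data will be analyzed following the ITT principle". It adds: "The imputation of missing values is not intended", with multiple imputation only as a possible sensitivity analysis.
- **Participant timeline {13}, Table 1:** randomisation is marked at T1, labelled "Day of progesterone supplementation". Transfer is at T3.
- **Who will be blinded {17a}:** "Both patients and researchers know the group assignments in the trial". Only the statisticians are blinded.
- **Withdrawal criteria {11b}:** unplanned withdrawal from transfer is a listed reason for leaving follow-up.
- **Adverse event reporting {22}:** medication is stopped when an adverse reaction occurs.
- **Endometrial preparation:** if the lining stays under 8 mm, "it should be discussed with patients whether to proceed with FET or abandon the protocol".

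**The concern.** Receiving a transfer is something that happens, or fails to happen, after allocation. Dividing by women transferred therefore conditions the primary comparison on a post-randomisation event, whereas ITT keeps every randomised woman in her arm. For a woman who withdraws before transfer, or whose medication is stopped for an adverse reaction, the two instructions give different answers. Nothing in the article says which one prevails.

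Two things are at stake. First, two analysts could report different primary results from the same data and both cite the protocol. Second, in an open trial where P+7 has one more day of progesterone before transfer than P+6, the share and the prognosis of untransferred women could differ by arm. The groups compared would then no longer be those formed by randomisation.

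**Working it through.** **1. The plan's own figure.** Inputs from Sample size {14}: 49% and 60%, two-sided alpha 0.05, power 0.90, 1:1, 5% loss.

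n per arm = [1.960·√(2p̄(1−p̄)) + 1.282·√(p1(1−p1) + p2(1−p2))]² / (p2−p1)², with p1 = 0.49, p2 = 0.60 and p̄ = 0.545.

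This gives 428.6, so 429 against the stated 430. The figure reproduces. The 49% comes from transfer cycles, so the calculation is on the per-transfer scale.

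**2. Power with all randomised women as denominator.** Assume a share c in each arm has no transfer and counts as not pregnant, and that those transferred keep the planned rates. The rates become 0.49(1−c) and 0.60(1−c), with 450 per arm.

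Power = Φ[(difference − 1.960·SE0)/SE1], where SE0 uses the pooled rate and SE1 the separate rates. For c = 5%: (0.1045 − 1.960 × 0.03331)/0.03313 = 1.18, giving 88.2%.

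| c (assumed) | Rates | Power at 450 per arm | n per arm for 90% |
|---|---|---|---|
| 0% | 49.0% vs 60.0% | 91.3% | 429 |
| 2% | 48.0% vs 58.8% | 90.1% | 448 |
| 5% | 46.6% vs 57.0% | 88.2% | 479 |
| 10% | 44.1% vs 54.0% | 84.5% | 534 |

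For comparison, if the planned 5% loss is all non-transfer, the per-transfer analysis has 450 × 0.95 = 427.5 per arm and 89.9% power.

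**3. Possible bias of the per-transfer rate.** Assume transfer day has no effect: every arm would reach 49% if all its women were transferred. Assume also that the women who miss transfer would have had a 20% chance. With a share e lost, the per-transfer rate is (0.49 − 0.20e)/(1−e). Type I error is the chance of two-sided p < 0.05 when the test statistic is shifted by bias/SE, with 450(1−e) women left in each arm.

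| Lost P+6 vs P+7 (assumed) | Per-transfer rates | Bias, points | Type I error |
|---|---|---|---|
| 5% vs 5.83% | 50.5% vs 50.8% | 0.3 | 5.1% |
| 5% vs 10% | 50.5% vs 52.2% | 1.7 | 7.8% |
| 0% vs 10% (worst case) | 49.0% vs 52.2% | 3.2 | 15.6% |

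The first row makes loss proportional to days on progesterone: 5% × 7/6 = 5.83%. In the last row the shift is 0.0322/0.0342 = 0.94 standard errors. With equal loss and equal prognosis in both arms the bias is zero.

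**4. Timing in Table 1.** T1 carries both randomisation and the label for the day of progesterone. T2, the HRT-cycle period, carries the pelvic ultrasound and stands after T1. Endometrial preparation puts the lining check, and the decision whether to go on, before progesterone. Going by the label, lining-related cancellations come mainly before randomisation. Going by the column order, some would come after it.

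**The case against.** The strongest reply is that the conflict may matter little in practice. The article gives no share of untransferred women. If randomisation takes place on the day progesterone starts, only a few days remain in which to miss transfer. The sole arm difference the documents establish is one further day of treatment, and loss in proportion to days moves type I error only to 5.1%. The sample size reproduces and already allows 5% for loss. All of this stands, and it limits what can be said about size. It does not remove the conflict, because the protocol itself fixes both the denominator and the principle.

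A reader might infer three stronger things that the documents do not support:

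- **That the primary result will be seriously biased.** The 15.6% needs P+6 to lose nobody, P+7 to lose 10%, and the lost women to have a 20% chance. No section supports any of these values.
- **That thin-lining cancellations inflate the problem.** T1 is already labelled as the day of progesterone, and the lining check precedes progesterone, so these are mainly exits before randomisation. T2 can also be read as the HRT days between progesterone start and transfer, since it also holds the serum hormone, compliance and adverse event entries. Only the column order is unclear.
- **That the sample size is miscalculated.** It is not, on the per-transfer scale on which it was computed.

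**Conclusion.** The point holds as a conflict of definitions in the primary outcome and in live birth. It should be settled before arm-level results are seen, because it decides which women count in the main comparison.

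The numerical consequence is unknown and may be small. Under the stated assumptions type I error runs from about 5.1% to 7.8% when both arms lose women, with 15.6% as a worst case. Moving to all randomised women puts power at 450 per arm at 90.1%, 88.2% or 84.5% for 2%, 5% or 10% untransferred.

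The per-randomised estimate answers a slightly different question. In the worst-case row it would be 0.49 − 0.10 × 0.20 = 47% against 49%, because pregnancies forgone through non-transfer count against the arm. That is the ITT question the protocol says it will answer.

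The Table 1 matter is minor. It is a request for clarification.

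**What to change.** 1. Define clinical pregnancy and live birth as the number of women with the event in the study cycle divided by all women randomised to the arm. Count a woman with no transfer as having no event. Her outcome is then known, so the statement against imputation is not affected.
2. Keep the per-transfer rate as a labelled sensitivity analysis, and report the number not transferred, with reasons, by arm.
3. Restate the power for the new denominator, with the assumed share of untransferred women given.
4. Reconcile the column order of Table 1 with the Endometrial preparation section, and state whether lining-related cancellations come before or after randomisation.

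**Cost.** Items 1 to 3 are changes of wording and reporting. No extra women are needed if power slightly below 90% is accepted. Holding 90% with 5% untransferred would need 479 per arm, or 2 × 479 − 900 = 58 more in total. Item 4 is wording only if women are already randomised after the decision to proceed. If they are not, any move of randomisation would change conduct in a trial that had enrolled more than 110 women when the article was written.

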#### Secondary outcome measures

Secondary outcome measures are the miscarriage rate and LBR.

Miscarriage rate: The ratio of the number of nonviable pregnancies before 12 weeks of gestation to the number of clinical pregnancies.

LBR: The ratio of the number of normal fetuses delivered after 28 weeks of gestation to the number of patients who received embryo transfer.

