### Sample size {14}

The sample size calculation is based on the clinical pregnancy rate. Retrospective data analysis (from January 2019 to December 2020, a total of 490 cycles of D6 single blastocyst transfer) showed that the clinical pregnancy rate of D6 single blastocyst transfer was approximately 49%. In our present study, we hope to improve the clinical pregnancy rate to 60%, the two-sided significance level will be set at *α* = 0.05, and the statistical power will be calculated as 1 − *β* = 0.90. The ratio between groups will be 1:1. The number of samples required for each group is 430. According to the 5% loss rate, there should be no fewer than 450 participants in each group, for a total of 900 participants.

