## Statistical methods

### Statistical methods for primary and secondary outcomes {20a}

SPSS 13.0 software was used for analysis. The *χ*^2^ test will be applied to detect the differences in counting data (such as the clinical pregnancy rate, implantation rate, and abortion rate). Comparison of the measurement data (such as age, the basic FSH level, the AFC, Gn dosage and days, the number of eggs taken, and the fertilization rate) between groups will be performed using an independent sample *t* test. A *P* value < 0.05 will be considered statistically significant.

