## Abbreviations

ART: Assisted reproductive technology
LBR: Live birth rate
FET: Frozen embryo transfer
HRT: Hormone replacement therapy
RCT: Randomized controlled trial
AE: Adverse event
hCG: Human chorionic gonadotrophin
LH: Luteinizing hormone
FSH: Follicle-stimulating hormone

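### The live birth rate divides fetuses by women, does not require live birth and rests on an undefined *normal*, so it is not a proportion of women with a live birth; the numerical effect is small

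*Protocol article*

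**What the plan says.** The section on secondary outcome measures states: "Secondary outcome measures are the miscarriage rate and LBR". The abbreviation list expands the term as "LBR: Live birth rate". The only definition is in the same outcomes section: "The ratio of the number of normal fetuses delivered after 28 weeks of gestation to the number of patients who received embryo transfer". No other section qualifies it, defines *normal*, or says how a multiple delivery is counted.

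The primary outcome uses a different unit. It is "the ratio of the clinical pregnancy (intrauterine gestation sac with a fetal heart beat) number to the number of patients who received embryo transfer", which counts pregnancies against women.

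Four other places bear on the point:
- Eligibility criteria {10}: one day 6 blastocyst is transferred.
- Who will be blinded {17a}: the trial is open, and only the statisticians are blinded.
- Statistical methods {20a}: a chi-square test is planned for count data, with "clinical pregnancy rate, implantation rate, and abortion rate" given as examples.
- Table 1, under Participant timeline {13}: secondary outcomes and a medical record review are scheduled after delivery.

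**The concern.** A live birth rate per transfer is normally read as the share of women who had a live birth. This definition differs from that in three ways.

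1. **Unit.** A woman who delivers twins adds 2 to the numerator and 1 to the denominator. The ratio is then not a proportion of women, and a chi-square test needs one independent yes/no result per woman.
2. **Vital status.** The text asks for delivery, not live birth. Read literally, a stillbirth after 28 weeks could enter the numerator.
3. **Normality.** On its plain reading, *normal* drops a live-born baby with an anomaly. Because the term is undefined and clinical staff know the allocation, a discretionary judgement enters an endpoint that could be objective.

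LBR is one of only two secondary outcomes and is named in the abstract. The background section motivates the trial partly with LBR results from earlier studies, so readers will set this trial's LBR beside theirs.

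**Working it through.** **Does any stated figure depend on the definition?** The document assumes no LBR. Its sample size rests on clinical pregnancy, 49% against 60%, two-sided 5%, power 90% (Sample size {14}). With pooled variance under the null, n per group is

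[1.960 × √(2 × 0.545 × 0.455) + 1.2816 × √(0.49 × 0.51 + 0.60 × 0.40)]² / 0.11² = (1.380 + 0.897)² / 0.0121 ≈ 429.

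The stated 430 reproduces, and LBR plays no part in it.

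**Assumed inputs (not in the document).** Share of women delivering, d = 40-50%. As a share of deliveries: twins t = 1-2%, stillbirths s = 0.5%, babies judged not normal a = 2-4%. The top of the range for d does not fit the control arm, because 50% exceeds the 49% clinical pregnancy rate assumed there.

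**Shift in one arm's rate, each effect alone**

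| Effect | Formula | d = 40% | d = 50% |
|---|---|---|---|
| Twins counted twice | d × t | +0.4 to +0.8 points | +0.5 to +1.0 points |
| Stillbirths counted | d × s | +0.2 | +0.25 |
| Not-normal babies removed | −d × a | −0.8 to −1.6 | −1.0 to −2.0 |

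**Net shift, d × (t + s − a), at d = 50%.** Lowest: 0.50 × (1 + 0.5 − 4)% = −1.25 points. Highest: 0.50 × (2 + 0.5 − 2)% = +0.25 points. At d = 40% the range is −1.0 to +0.2.

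**Effect on the difference between arms.** If the rates are the same in both arms, each arm's LBR is multiplied by (1 + t)(1 − a) + s.
- Twins alone at 2%: a true 5-point difference becomes 5 × 1.02 = 5.1.
- All three, t = 1%, a = 4%: 5 × (1.01 × 0.96 + 0.005) = 5 × 0.9746 = 4.87.
- All three, t = 2%, a = 2%: 5 × (1.02 × 0.98 + 0.005) = 5 × 1.0046 = 5.02.

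If unblinded judgement removed 2% of babies in one arm and 4% in the other, the spurious difference at d = 40% would be 0.40 × 2% = 0.8 points. For scale, with 450 women per arm the standard error of a difference near 40% is √(2 × 0.40 × 0.60 / 450) = 3.3 points.

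**Effect on the chi-square test (twins only, d = 40%).** Per-woman variance of the fetus count is d(1 + 3t) − d²(1 + t)². The test assumes p(1 − p) with p = d(1 + t).
- t = 1%: 0.2488 against 0.404 × 0.596 = 0.2408, ratio 1.033.
- t = 2%: 0.2575 against 0.408 × 0.592 = 0.2415, ratio 1.066.

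The actual size of a nominal 5% test is 2Φ(−1.96/√ratio): about 5.4% and 5.8%.

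**Per-woman definition.** Counting women with at least one live-born baby removes all three shifts and gives one binary value per woman.

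**The case against.** The case for leaving this alone is that LBR is secondary, the label itself says live birth, and with one blastocyst transferred, twins need embryo splitting or a concurrent conception. Both arms use the same rule. All of this stands, and it limits the size of the problem. It does not make the definition correct, because no other text repairs it.

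A reader might infer more than the document supports:

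- **That stillbirths certainly count and anomalous babies are certainly removed.** *Normal* may be loose wording meant to exclude stillbirths. What the text shows is an ambiguous term and a missing requirement of live birth, not settled rules.
- **That the comparison between arms is biased or the test invalid.** No mechanism for a large differential effect is given, and the distortion of the test is slight.
- **That live birth will go untested because the methods section does not name it.** That list is illustrative. Its mention of an implantation rate, which is not a defined outcome, is a separate minor inconsistency and says nothing about LBR.
- **That the result could not be combined with other studies.** If delivery records hold plurality and vital status, a per-woman rate can be recovered.
- **That the denominator must become all women randomised.** Whether a transferred-patient denominator fits the stated ITT principle is a separate question, which the defects described here do not settle.

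**Conclusion.** The definition is wrong as written: it mixes fetuses with women, does not explicitly require live birth, and depends on an undefined term applied in an open trial. It should be corrected. Severity is moderate, not must-fix.

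Under the assumed rates, no single effect exceeds about 2 points in an arm, the effects partly offset, and most of what remains is common to both arms. The chi-square test is only slightly anti-conservative. The stillbirth and anomaly components also depend on how *normal* is read; the double counting of twins follows directly from the wording. The primary outcome, its analysis and the sample size are untouched.

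**What to change.** Define LBR as the number of women with at least one live-born baby after the stated 28-week threshold, one yes/no value per woman, divided by the trial's chosen analysis denominator. Delete *normal*. Count a multiple delivery once. Report stillbirth, congenital anomaly and multiple birth separately, by arm.

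The cost is a short wording amendment plus a little data work. Table 1 already schedules secondary outcomes and a record review after delivery, but it does not list vital status or plurality as items. The delivery record must capture both, along with any anomaly to be reported. The change should be made before outcome data are analysed.

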### Participant timeline {13}

The participant timeline is shown in Table1.

**Table 1 Tab1:** SPIRIT figure: schedule of enrollment, interventions, and assessments

Timepoint	Study period					
	Enrollment			Post-allocation		
	T1	T2	T3	T4	T5	T6
	Day of progesterone supplementation	Period of HRT-cycle	Day of embryo transfer	14 days after transfer	30/42 days after transfer	After delivery
**Enrollment:**						
Eligibility screen	X					
Informed consent	X					
Randomization	X					
Basic information login	X					
Physical examination	X					
Medical/treatment history	X					
Pelvic ultrasound		X			X	
Serum E2, P level		X				
**Intervention:** Embryo quality			X			
**Data collection:**						
Serumβ-hCG level				X		
Primary outcome measure					X	
Secondary outcome measures					X	X
Compliance assessment		X	X			
Adverse events		X	X			
Medical record review					X	X

### Sample size {14}

The sample size calculation is based on the clinical pregnancy rate. Retrospective data analysis (from January 2019 to December 2020, a total of 490 cycles of D6 single blastocyst transfer) showed that the clinical pregnancy rate of D6 single blastocyst transfer was approximately 49%. In our present study, we hope to improve the clinical pregnancy rate to 60%, the two-sided significance level will be set at *α* = 0.05, and the statistical power will be calculated as 1 − *β* = 0.90. The ratio between groups will be 1:1. The number of samples required for each group is 430. According to the 5% loss rate, there should be no fewer than 450 participants in each group, for a total of 900 participants.

### Recruitment {15}

Potential participants will be recruited from Nanjing Drum Tower Hospital (Nanjing, China), which is qualified for FET. Our study will be propagated via the internet, bulletin boards, and posters in hospitals, with a hotline provided for potential volunteers to call. Eligible patients from the outpatient department will be asked to talk face to face with researchers and will be given detailed information about the study. If patients are eligible and interested in participating, they will be asked to sign an informed consent form. The recruitment period is from July 2021 to June 2024, and the estimated recruitment rate is more than 95%.

## Assignment of interventions: allocation

### Sequence generation {16a}

A 1:1 allocation to either group A or group B will be generated by Stata 15.0 (SPSS Inc., Chicago, IL, USA) and will be used for randomization.

